## Methods

### Design overview

Miracle Messages, the nonprofit that delivers the Miracle Friends and Miracle Money interventions, is headquartered in the San Francisco Bay Area but expanded to have staff members in Los Angeles for this study. Through partnerships with homeless service agencies or direct street outreach, Miracle Messages staff members engaged unhoused individuals to explain the Miracle Friends intervention, which requires having a phone, and signed up anyone who expressed interest in a phone buddy. Those who signed up also learned about a study to evaluate the Miracle Friends intervention, and those who expressed interest were referred to a study team affiliated with the University of Southern California. For those who agreed and provided written informed consent to participate in the study, a random number generator was used to determine sequentially whether a study participant would be offered the Miracle Friends intervention or put on a waitlist. Participants were told that they had a two-thirds chance to be offered Miracle Friends but were not told that approximately half of those offered Miracle Friends would be assigned to a third arm of the study that could receive basic income. For this group, receiving basic income through Miracle Money was contingent on participating in Miracle Friends. Figure 1 depicts how participants were randomized using a parallel-group trial design to one of three groups with a 1:1:1 allocation ratio: (a) those offered Miracle Friends only; (b) those who would be offered Miracle Money if they participated in Miracle Friends; and (c) those on a waitlist for Miracle Friends. Recruitment continued until at least 100 people began receiving Miracle Money.

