***Other covariates***	
Demographic and historic information (baseline only)	The baseline survey includes questions about the following demographic and historic information taken from previous research studies related to homelessness: age, sex, gender, sexual orientation, race and ethnicity, country of origin, relationship status, children, level of education, military service, health insurance, public benefits, employment, monthly income, criminal justice involvement, homeless history, housing preferences, and health conditions
Employment status	Employment status is measured using questions from the Los Angeles County Homeless Count demographic survey [51]. Participants are asked, “What is your employment status?” with the following response options: Employed, full-time (35 h a week or more); Employed, part-time; Unemployed, looking for work; Unemployed, not looking for work; Retired, receiving retirement benefits; and Retired, not receiving benefits. Participants are also asked to indicate their total monthly income
Financial well-being	Adapted questions from the Consumer Finance Protection Bureau’s abbreviated 5-item measure are used. Questions include: “Usually, do you have enough money to meet your needs?” with response options: Completely; Mostly; Moderately, A little; Not at all. “How often (always, often, sometimes, rarely, never) does this statement apply to you? (1) I have money left over at the end of the month; and (2) My finances control my life.” “How well (completely, very well, somewhat, very little, not at all) do the following statements describe you or your situation? (1) Because of my money situation, I feel like I will never have the things I want in life; (2) I am just getting by financially; and (3) I am concerned that the money I have or will save won’t last.” Participants are also asked if and what health insurance they have; monthly benefits that they receive (e.g., general relief, social security disability income or Supplemental Security Income; Supplemental Nutritional Assistance); if they have a bank account; and whether they were able to pay all bills last month

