### Quantitative data analysis

#### Social isolation outcomes

To evaluate the efficacy of the Miracle Friends intervention on social support, psychological distress, and loneliness, we will use responses to the Oslo Support Scale [53], Kessler Psychological Distress Scale [55], and UCLA Loneliness Scale [52], respectively, at the final survey (Quarter 5). Each measure will first be summed to develop a total score, then dichotomized based on cutoffs for each measure based in the literature—i.e., poor social support will be coded as 1 if the Oslo Support Scale sum score is less than 9 (indicative of poor social support) and 0 otherwise; psychological distress will be coded as 1 if the Kessler Psychological Distress Scale sum score is greater than 25 (indicative of high psychological distress) and 0 otherwise; and loneliness will be coded as 1 if the UCLA Loneliness Scale sum score is greater than or equal to 6 (indicative of high loneliness) and 0 otherwise. Each dichotomized score will be modeled as a function of treatment group (1 = Miracle Friends or Miracle Money group members who participated in at least one phone buddy intervention, 0 = waitlist group); covariates including demographic characteristics, physical and mental health, and substance use; and a random intercept for city in random intercept logistic regression models.

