#### Statistical power

To reach a target goal of 105 participants receiving basic income through Miracle Money, recruitment efforts have yielded more than 200 individuals in each treatment group. Assuming that each arm will have at least 105 participants, our study can detect the hypothesized 50% difference in proportion of people exiting homelessness at Quarter 5 between the Miracle Money and waitlist group (assuming 60% of the Miracle Money group exits homelessness and 10% of the waitlist group exits homelessness) using a *p*-value threshold of 0.05 with power exceeding 95%. When comparing the Miracle Friends group to the waitlist group, our study can detect the hypothesized 15% difference in proportion of people exiting homelessness at Quarter 5 between the Miracle Friends and waitlist group (assuming 25% of the Miracle Money group exits homelessness and 10% of the waitlist group exits homelessness) using a *p*-value threshold of 0.05 with power exceeding 60%. Differences in proportions of the social isolation outcomes will be detected at powers identical to the housing outcome, assuming identical differences in proportions and *p*-values. Regarding the effect modification of treatment by race in exiting homelessness, our study will be able to detect a difference in proportion of groups exiting homelessness of 35% with power exceeding 20%. Main effect calculations were done on unadjusted models using the WebPower R package, and the effect modification power calculations were performed via simulation.

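### Loneliness, social support and distress are analysed only as 0/1 cut-offs, with no baseline score named as covariate: an avoidable loss of precision, not a bias

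*Protocol article*

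**What the plan says.** The Social isolation outcomes section takes each scale's total at the final survey, "then dichotomized based on cutoffs for each measure based in the literature". The cut-offs are below 9 for Oslo, above 25 for Kessler and 6 or more for UCLA. Each binary variable goes into a logistic model with a random intercept for city. Treatment is coded as members of either intervention arm who took part in the phone-buddy programme, against the waitlist. No analysis of the full scores is stated.

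The adjustment set is described as "covariates including demographic characteristics, physical and mental health, and substance use". Neither the baseline loneliness score nor the baseline support score is named, and no time point is given for the health and substance-use covariates.

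Table 1 lists housing status, loneliness and social support as primary outcomes. The Kessler scale stands under the other covariates but is analysed alongside them. Only one row of the table is marked as baseline only ("Demographic and historic information (baseline only"). The data-collection section says that the shorter quarterly survey covers topics similar to those at baseline. The scales therefore appear to be measured at both.

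The Statistical power section treats these outcomes as proportions, on unadjusted models, and carries over the power figures for housing.

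**The concern.** The first research question is whether Miracle Friends goes with less isolation and more support, which is a matter of degree. Scored 1 to 3 per item, UCLA runs from 3 to 9. A participant at 9 and one at 6 at Quarter 5 are coded alike, while 6 and 5 are coded as opposites. Oslo (4 + 5 + 5 response levels, 3–14) and Kessler (ten five-level items, 10–50) are collapsed in the same way.

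A participant's own baseline score is usually a strong predictor of the follow-up score. If it is collected and not used, further precision is given up.

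What is at stake is the chance of detecting a real effect on two primary outcomes. It is also at stake for the race-by-treatment interaction, which is added to every model and for which the protocol claims only more than 20% power on housing.

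**Working it through.** **1. The plan's own power figure.** Inputs from Statistical power: "Assuming that each arm will have at least 105 participants", and 25% against 10% for the smaller contrast. The sentence concerns Miracle Friends but prints Miracle Money: "assuming 25% of the Miracle Money group exits homelessness and 10% of the waitlist group exits homelessness". Two-sided 5% is assumed, because sidedness is not stated.

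- Pooled SE = √(2 × 0.175 × 0.825 / 105) = 0.0524
- Unpooled SE = √((0.25 × 0.75 + 0.10 × 0.90) / 105) = 0.0514
- Power = Φ((0.15 − 1.96 × 0.0524) / 0.0514) = Φ(0.92) ≈ 82%

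The stated figure ("value threshold of 0.05 with power exceeding 60" per cent) is therefore true as a lower bound, but it is not the value. About 60% would need about 63 per arm, or 76 with continuity correction. The larger contrast, 60% against 10%, gives over 99.9%, consistent with the stated figure of more than 95%.

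**2. Loss from dichotomising alone.** For a normal score cut at prevalence p, efficiency relative to the full score is φ(z_p)² / [p(1 − p)].

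| Prevalence p | Calculation | Efficiency | Loss |
|---|---|---|---|
| 50% | 0.399² / 0.25 | 0.637 | 36% |
| 25% or 75% | 0.318² / 0.1875 | 0.539 | 46% |
| 10% or 90% | 0.175² / 0.09 | 0.342 | 66% |

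The real scales are coarser than a normal score. Simulated item-level scores, cut where the plan cuts them, lose 27–47% for loneliness, 34–46% for support (approximated with five levels on every item) and 34–40% for distress. Simulated prevalences run from about 19% to 80%, and the 47% arises at 80%.

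**3. Adding the baseline score.** Adjusting for a baseline score with correlation r multiplies the residual variance by 1 − r². With r = 0.5 (assumed), the combined loss is:

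- at 50% prevalence: 1 − 0.637 × 0.75 = 52%
- at 25% prevalence: 1 − 0.539 × 0.75 = 60%

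**4. In terms of power, 105 against 105.**

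- 40% against 55% implies a latent difference of 0.379 SD. Power is 59% binary. For the full score it is Φ(0.379 × √(105/2) − 1.96) = Φ(0.79) = 78%. Adjusted at r = 0.5 it is 89%.
- 25% against 10%, the rates carried over from housing, implies 0.607 SD. Power is 82% binary against 99% full score; for 80% power the required n per arm is 100 against 43.

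**5. In terms of the comparison the plan specifies.** The isolation models pool both intervention arms, so 105 against 105 is not the planned contrast. The Results section reports 360 matched and 233 on the waitlist (the abstract has 237). Matched is an upper bound for those with phone-buddy contact. Half of each, an assumed 50% loss, is 180 and about 117.

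The simulation uses a three-item 3–9 score with item loading 0.8, a latent shift of 0.45 SD, and about 52% of the waitlist and 36% of the treated at 6 or above. The latent baseline correlation is varied from about 0.4 to 0.7.

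| Sample | Cut-off | Sum score | Sum score + baseline |
|---|---|---|---|
| 105 vs 105 | about 64% | about 80% | 83–89% |
| 180 vs 117 | about 77% | about 90% | 92–96% |

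**The case against.** The cut-offs are fixed numerically in advance, are said to come from the literature, and agree with the binary housing outcome and the proportion-based power statement. There is no contradiction and no bias. That stands: this is a point about efficiency.

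The covariate list is open-ended, mental health might include baseline distress, and an article may leave the full list to the analysis plan. That also stands. The fair statement is that the baseline loneliness and support scores are not named; a reader might infer that they have been excluded, but the document does not say so. Baseline collection is itself inferred from Table 1 and the survey description, since the schedule figure is not shown. The comparisons above also set an unadjusted cut-off test against an adjusted score, whereas the plan's model adjusts for other covariates that may recover part of the gain.

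The pooled comparison may have ample power in any case: at 52% against 36%, the binary test reaches 97% with 360 and 233, and 90% with 252 and 163 (30% lost). This weakens any claim that the trial is underpowered. It leaves the proportional loss untouched, because that does not depend on n, and the loss still counts for the width of the intervals and for the interaction with race.

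A reader might infer from the power section that the first question has only about 60% power. It does not support that. The 60% is a lower bound for a Friends-only housing contrast that recomputes to 82%, and it carries over only if the proportions are identical.

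**Conclusion.** The point holds as an avoidable loss of precision in two primary outcomes and in distress. The dichotomy is a stated choice, not detail left to another document. The baseline score is the secondary part and holds only in the sense that it is not named.

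No single percentage can be read from the protocol. Which part of the range in the working applies depends on the prevalence at the cut-off, the spread of each score and the baseline correlation, none of which is given. The power simulation covers the loneliness scale only. On its assumptions, the sum score gains about 13 percentage points over the cut-off at 180 against 117 (90 − 77), and baseline adjustment a further 2 to 6.

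A reader might go further and conclude that the planned results would be biased or the trial underpowered for isolation. The document supports neither. Whether participants should be compared by assignment or by participation is a separate question, and this point does not depend on it.

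**What to change.** In the Social isolation outcomes section, make the primary analysis of each scale the Quarter 5 sum score, in a linear or proportional-odds model that keeps the city term. Adjust for the participant's own baseline score on that scale. State that the physical health, mental health and substance-use covariates are taken at baseline, because follow-up values could absorb part of the treatment effect and overlap with the distress outcome. Keep the three cut-offs as a supportive display of proportions.

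The cost is wording. A mean difference or common odds ratio is slightly harder to communicate than a proportion, which the retained display covers. The proportion-based power statement would need rewording for these outcomes, with the assumed standard deviation and baseline correlation stated.

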**Results:**

Of 760 unhoused individuals enrolled in the study, 256 were randomized to receive Miracle Friends, 267 were randomized to receive Miracle Money, and 237 were randomized to the waitlist control group. In the two intervention groups, 360 of 523 unhoused individuals were initially matched to a phone buddy. Of the 191 study participants in the Miracle Money group who had been initially matched to a volunteer phone buddy, 103 were deemed to be participating in the program and began receiving monthly income.

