#### Miracle money

Whereas the Miracle Money proof-of-concept provided $500 for 6 consecutive months, for this study, funds were raised so that Miracle Messages could provide up to 110 individuals with $750 per month for 12 months. This was based on pilot work that suggested that $500 per month meaningfully changed lives [41] but recognition that a living wage in these cities would be much higher [48]. As noted, Miracle Money is not advertised to those interested in the Miracle Friends intervention; unhoused individuals are only notified about the possibility of receiving basic income if they are randomized to the Miracle Money condition and participate in the Miracle Friends interventions. Although participation was defined as having had at least two contacts with a matched volunteer in a 1-month period, at the outset of the study there were efforts to ensure that the two contacts could be characterized as “meaningful” based on volunteer feedback to help ensure that the matching process would result in a prolonged friendship or relationship. Yet because many of the initial contacts could not be confirmed to be meaningful, Miracle Messages increasingly came to accept any type of contact with volunteers as meeting the criteria of Miracle Friend participation that would then allow participants to start receiving Miracle Money.

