#### Housing outcomes

The association of Miracle Friends with housing outcomes will be evaluated using logistic regression with a random intercept, modeling the dichotomized outcome of exited homelessness (1 = individual responded “My own apartment or home” or “Someone else’s apartment or home,” 0 = otherwise) as a function of treatment (1 = Miracle Friends group members who participated in at least one phone buddy intervention, 0 = waitlist group), with the same covariates and random intercept.

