#### Differences in treatment effect based on race

To evaluate if outcomes differ by race, all models will be run with the addition of an interaction between race and treatment.

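### Every specified outcome model compares only intervention members who engaged with the whole waitlist arm, so the contrast is not the randomised one and can be biased

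*Protocol article*

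**What the plan says.** Under Quantitative data analysis, Social isolation outcomes, the treated category is "Miracle Friends or Miracle Money group members who participated in at least one phone buddy intervention". The reference category and adjustment follow: "0 = waitlist group); covariates including demographic characteristics, physical and mental health, and substance use", plus a random intercept for city.

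Under Housing outcomes the coding is "1 = Miracle Friends group members who participated in at least one phone buddy intervention, 0 = waitlist group", with the same covariates and random intercept. In the first sentence the participation clause might be read as qualifying only the Miracle Money members. The housing sentence attaches it to Miracle Friends members alone, which settles the reading.

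The section on race says that "all models will be run with the addition of an interaction between race and treatment", so the same coding carries over.

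The article specifies no comparison of all randomised participants by assigned arm, no complier-average estimate and no sensitivity analysis on this point. The Discussion promises only a later comparison of people who engaged with people who did not.

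On uptake, the Abstract reports that "360 of 523 unhoused individuals were initially matched to a phone buddy". The Results section splits the 360 into 169 in Miracle Friends and 191 in Miracle Money. It adds that 56 people were still unmatched, that 103 could not be contacted after assignment, and that 103 Miracle Money members were verified as participating.

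**The concern.** Allocation was 1:1:1 and preceded any contact with a volunteer. Engagement comes afterwards. Under Interventions, Miracle friends, a person is taken off the matching list after repeated failed contact attempts. In the Discussion the authors link failure to reach referred people to instability in their lives. Stability plausibly predicts housing, and sociability plausibly predicts loneliness and support.

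Removing non-engagers from one side only therefore compares a selected part of the intervention arms with an unselected control arm. The listed covariates cover demographics, health and substance use. None measures reachability or willingness to engage, so they cannot be relied on to restore balance. If engagers would have done better anyway, the models would credit the programme with that advantage. The article's stated aim, to learn from a randomised trial whether the programmes reduce isolation and improve housing, would then rest on an observational contrast.

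**Working it through.** **Inputs.** Randomised: 256 Friends, 267 Money, 237 waitlist (Abstract). The Results section gives 233 for the waitlist, but only 237 makes the arms sum to 760. Matched: 169, 191 and 360 in total. Housing exit rates (Statistical power): 10% waitlist, 25% Friends, 60% Money. The article's sentence on the Friends comparison labels the 25% as Money. Assumed, because the article gives no figures: outcomes of engagers relative to non-engagers, prevalence of the isolation outcomes, and retention. All tests are two-sided pooled z-tests at 0.05, unadjusted.

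**The plan's own power figures.** At 105 per arm, 25% vs 10% gives 82% and 60% vs 10% gives over 99.9%. The stated bounds (over 60% and over 95%) are true, the first loosely. The point does not depend on them.

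**Share excluded.**
- Unmatched: 523 − 360 = 163, and 163/523 = 31%. By arm: 87/256 = 34% Friends and 76/267 = 28.5% Money.
- If all 56 still waiting are matched and take part: 163 − 56 = 107, and 107/523 = 20%.
- If matched people never take part, the share is higher. Verified participation in Money was 103/267 = 38.6%.

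**Bias in housing with no true effect.** Let f = 169/256 = 0.660, overall exit rate 10% in every arm, and R the ratio of engagers' to non-engagers' exit rates. Non-engagers exit at 0.10/(f·R + 1 − f), and engagers at R times that. For R = 2: 0.10/(1.320 + 0.340) = 6.0% and 12.0%. Engagers (169) are tested against the waitlist (237):

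| R | Engagers | Non-engagers | Spurious difference | Rejection |
|---|---|---|---|---|
| 1 | 10.0% | 10.0% | 0 | 5% |
| 1.5 | 11.3% | 7.5% | +1.3 points | 7% |
| 2 | 12.0% | 6.0% | +2.0 points | 10% |
| 3 | 12.9% | 4.3% | +2.9 points | 16% |

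**Bias in an isolation outcome with no true effect.** Assumed prevalence 50%. Bias = (share excluded) × (gap between engagers and non-engagers).
- 360 vs 237, 31.2% excluded: a 10-point gap gives 3.1 points and 12% rejection; a 20-point gap gives 6.2 points and 32%.
- 416 vs 237 (all 56 added), 20.5% excluded: 2.0 points and 8%; 4.1 points and 17%.

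**Power when analysed by assigned arm, housing.**
- Friends, non-engagers at 10%: 0.660 × 25% + 0.340 × 10% = 19.9% vs 10%. With 256 vs 237, power is 87% at full follow-up and 66% at 60% retention.
- Friends, non-engagers at 3.4%: 0.660 × 25% + 0.340 × 3.4% = 17.7% vs 10%. Power is about 70% and 48%.
- Money, non-recipients at 10%: 0.386 × 60% + 0.614 × 10% = 29.3% vs 10%. Power is about 97% at 50% retention, and lower if non-recipients exit at under 10%.

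**What each estimate recovers.** Take the 3.4% case. With no treatment, engagers would exit at 13.4%, since 0.660 × 13.4% + 0.340 × 3.4% = 10%. If treated engagers exit at 25%, their true gain is 11.6 points. The engaged-only contrast shows 25 − 10 = 15 points, of which 3.4 is selection. The assigned-arm difference is 7.7 points, and 7.7/0.660 is about 11.6, the gain among engagers.

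**The case against.** Several stronger statements are tempting, and the article does not support them.

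- **That the effects are certainly biased.** The article has no outcome data by engagement, and the models adjust for some prognostic factors. Part of the non-engagement is programme-side: the Discussion says matching was sometimes delayed for want of volunteers, and exclusions of that kind need not be prognostic. The 56 still waiting are 34% of the 163. What is certain is the loss of randomised protection; the size of any bias is not.
- **That at least 31% are excluded.** Matching was reported at one date and people may re-enrol, so the share could fall to about 20% or rise.
- **That the waitlist loses nobody.** Outcomes come from the Quarter 5 survey, and Limitations names retention as a challenge. Unreachable waitlist members will also tend to be missing, which may narrow the imbalance by an amount that cannot be computed.
- **That 20-point gaps apply to housing.** With f = 0.660 and a 10% base rate, non-engagers would sit at −3.2%. The largest possible bias is 10/0.660 − 10 = 5.1 points. Even a 10-point gap (13.4% vs 3.4%, about a fourfold ratio), which gives 19% rejection, is steep.
- **That the analysis threshold contradicts the programme's own.** The Miracle money section says that "participation was defined as having had at least two contacts with a matched volunteer in a 1-month period", but there this decides when payments start. It is not an analysis definition, and a looser analysis threshold excludes fewer people.
- **That the repair is almost free.** Power of 87% assumes non-engagers do as well as the waitlist, which is to assume no selection.

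These objections reduce the size and the certainty. None supplies a randomised comparison, and the coding is a rule the article states, not a detail left to an analysis plan.

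**Conclusion.** The point stands as a defect in the stated rule. Each specified outcome model, covering all three primary outcomes, replaces the randomised contrast with engagers against the whole waitlist, and nothing else in the article restores it. Bias is plausible, most likely in the programme's favour, but neither direction nor size can be established from the article. Under the assumptions shown, false-positive rates range from 7–16% for housing and from 8–32% for a 50%-prevalence outcome, against a nominal 5%. They return to 5% if engagement is unrelated to outcome. These figures are unadjusted and assume that every matched person participates and that follow-up is complete.

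**What to change.** For every outcome, make the primary analysis compare all randomised participants by assigned arm, whether or not they were matched or engaged. State how missing Quarter 5 outcomes will be handled, because people who cannot be contacted will often have none. Keep the engagement question as a secondary complier-average effect with assignment as the instrument. Non-compliance is essentially one-sided, since waitlist members have no access for 15 months unless they withdraw. The estimate also needs the assumption that assignment acts only through engagement. Label any engaged-only contrast exploratory.

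No new recruitment or survey round is needed, because all participants are surveyed regardless of arm. The price is a diluted estimate, the need for missing-data assumptions, and power that depends on how non-engagers fare. For Friends this can fall below the article's stated 60% if retention is poor and non-engagers do worse than the waitlist.

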To better understand the impact of the Miracle Friends intervention and how adding basic income influences outcomes, the Miracle Messages nonprofit and the University of Southern California Suzanne Dworak-Peck School of Social Work established a community–academic partnership in 2022 to design and conduct a randomized controlled trial of these interventions. Through private philanthropy, funding was secured to provide basic income to as many of 105 individuals for 1 year. The study takes place in the Los Angeles and San Francisco Bay areas of California, which have high rates of homelessness. California accounts for 30% of all people in the USA experiencing homelessness, including half (*n* = 115,491) of all unsheltered people, many of whom reside in the Los Angeles and San Francisco Bay areas [39]. In these urban regions and nationally, African Americans are overrepresented in the homeless population. Nationally, African Americans comprise 40% of the homeless population while representing only 13% of the general population [39]. This is an important factor to consider for this study, because although Whites are more likely to become homeless due to individual risk factors such as health impairments or disabilities, research suggests that African Americans are more likely to become homeless due to lack of income and social capital [43], both of which are target outcomes for the Miracle Money intervention [44]. However, it is unclear whether increased income and social support can overcome other forms of discrimination experienced by African Americans that may be required to exit homelessness [45].

The overarching research questions that this study seeks to answer are: (1) Is the Miracle Friends intervention associated with reduced social isolation and increased social support? (2) Is the Miracle Friends intervention associated with improved housing outcomes? (3) Does the addition of basic income through the Miracle Money intervention improve these outcomes of interest? (4) Are there differences in outcomes based on race?

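### The random intercept for city probably has only two levels, so its variance cannot be estimated reliably and the planned site adjustment will often drop out; a fixed effect for area is better

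*Protocol article*

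**What the plan says.** In the Protocol article, Social isolation outcomes, each dichotomised score is modelled on treatment group, covariates and "a random intercept for city in random intercept logistic regression models". Housing outcomes uses a logistic model "with the same covariates and random intercept". The section on race adds an interaction to all of these models, so every planned quantitative model carries the city term.

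On the number of places, the Background states: "The study takes place in the Los Angeles and San Francisco Bay areas of California". Design overview says that the programme "is headquartered in the San Francisco Bay Area but expanded to have staff members in Los Angeles for this study". The Miracle money section, explaining the size of the payment, remarks that "a living wage in these cities would be much higher". The article neither lists nor counts cities, and it gives no fallback for a variance estimated as zero.

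Randomisation was of individuals: "a random number generator was used to determine sequentially". The article mentions no stratification by area.

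**The concern.** On the natural reading, city means Los Angeles versus San Francisco Bay. A random intercept treats its levels as draws from a distribution and estimates that distribution's variance. Two draws leave one degree of freedom, so the estimate is often exactly zero and is otherwise very imprecise. At zero, the fitted model is an ordinary logistic regression without any area term, although the report would describe it as adjusted for city.

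This would hardly matter in a comparison of all randomised participants. The planned contrast differs: the treated group is limited to intervention members with at least one phone-buddy contact, and they are compared with the waitlist group. Only 360 of 523 intervention participants (69%) were initially matched, and the Discussion reports matching delays when volunteers were short. If matching success differed by area, the compared groups would differ in area mix. The article does not say whether it did.

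**Working it through.** **The plan's own figures.** The article gives no number of cities and no between-city variance, so there is no stated figure on this point to reproduce. Its main-effect power figures come from unadjusted models without a city term. Recomputed at 105 per arm, 60% vs 10% gives above 99.9% (stated: above 95%), and 25% vs 10% gives 82% two-sided (stated: above 60%). Both statements hold as lower bounds, and neither bears on the city term.

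**Inputs.**
- Sample size: Statistical power works from "Assuming that each arm will have at least 105 participants". I used 105 to 200 participants per area in the closed form and 420 in total in the simulation.
- Event rates: the article's 10% vs 25% and 10% vs 60%. The averages are (10 + 25)/2 = 17.5% and (10 + 60)/2 = 35%.
- Assumed, because the article gives neither: between-site SD τ of 0 to 0.5 on the logit scale, and an even split between areas.

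**Closed form for two equal areas.** The sampling variance of each area's log odds is s² = 1/(n·p·(1−p)). The observed difference D between areas has variance 2(s² + τ²). The ML variance estimate is max(0, D²/4 − s²). It is therefore zero when a χ² variable on 1 df falls below 2s²/(s² + τ²). For a REML-type estimate the bound is s²/(s² + τ²).

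Example with n = 105, p = 0.175, τ = 0.2:
- s² = 1/(105 × 0.175 × 0.825) = 0.0660.
- The bound is 0.1319/(0.0660 + 0.04) = 1.245.
- The probability of a zero estimate is 0.74.

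At the other end, with n = 200, p = 0.35, τ = 0.5: s² = 0.0220, the bound is 0.0440/0.2720 = 0.162, and the probability is 0.31.

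**Simulation.** Random-intercept logistic model, ML with 25-point quadrature, rates 10% vs 25%, 200 runs per setting. Near zero means an estimated SD below 0.02.

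| True SD | ML zero, closed form | REML-type zero | Simulated near zero, 2 cities | Simulated near zero, 10 cities |
|---|---|---|---|---|
| 0 | 84% | 68% | 85% | 67% |
| 0.2 | 60–74% | 45–57% | 69% | 49% |
| 0.3 | 47–64% | 34–49% | not run | not run |
| 0.5 | 31–48% | 22–35% | 37% | 11% |

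With two cities and a true SD of 0.5, the estimates ran from 0 to 1.0 (5th to 95th percentile). On 1 df, a 95% interval for the SD runs from about 0.45 to 32 times the estimate.

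**Effect on the treatment estimate, balanced areas.** At SD 0, 0.2 and 0.5, the mean log odds ratio was 1.125, 1.112 and 1.116 with the random intercept and 1.127, 1.115 and 1.120 with a fixed area indicator. The mean absolute difference was 0.002 to 0.003, and the empirical standard errors were practically identical (0.26 to 0.30).

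**Effect with unequal area mix.** Take a true site difference of 0.3 in log odds, at which the term drops out in about 60% of trials. A rough size is imbalance × site difference × chance of dropping out:
- 10 points: 0.10 × 0.3 × 0.6 = 0.018.
- 30 points: 0.30 × 0.3 × 0.6 = 0.054.

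Direct simulation gave about 0.015 to 0.06. I re-ran it with 210 per group and 400 runs per setting. At a site difference of 0.3, the random-intercept and fixed-effect estimates differed by 0.015 (10 points) and 0.061 (30 points). At differences of 0.5 and 0.7, they differed by 0.016 to 0.018 and by 0.069 to 0.074. The fixed effect lost no meaningful precision.

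**The case against.** Four points on the other side have force.

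- **City is undefined.** The two-level reading is an inference from the areas named. If city meant municipalities, the problem shrinks: with ten, the near-zero share at SD 0.5 falls from 37% to 11%. A condensed article may leave the definition to the full plan. This stands as a condition on the point. It does not remove it, because the random intercept itself is a stated choice and only two places are named.
- **The failure partly cancels itself.** The ML variance is zero only when the observed difference is below 2s, which is |z| below about 1.41. The term therefore drops out when the data show little difference between areas. The largest difference dropped is 2 × √0.0220 = 0.30 to 2 × √0.0660 = 0.51 across the inputs used. This stands, and it is why the effect is small.
- **No research question concerns between-city variance.** Its poor precision affects no stated inference directly. This also stands. The harm comes only through lost adjustment.
- **The simulations simplify the planned analysis.** The even split and the SDs are assumptions, and covariates and attrition are left out. This stands, which is why ranges are given.

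A reader might infer that the variance cannot be estimated at all, or that every model will be singular or depend on software. Neither follows. The model can be fitted, the variance is formally identifiable, and at SD 0.5 about 63% of the simulated fits were not near zero.

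**Conclusion.** The point holds as a minor specification flaw, provided that city has two levels. The variance then cannot be estimated reliably, and the site adjustment that the plan promises drops out in roughly 30% to 75% of trials for between-site SDs of 0.2 to 0.5.

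The documents do not support reading this as a threat to the main result. With areas balanced between the compared groups, the shift in the log odds ratio is negligible. With an assumed imbalance of 10 to 30 points it stays small, at most about a quarter of a standard error (0.074/0.29) in the most unfavourable setting tried. The between-site SD, the even split and the imbalance are all assumptions. What decides the matter is that a fixed effect always adjusts for area and costs practically no precision.

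**What to change.** State what city means and how many levels it has. If it has two, replace the random intercept with a fixed effect for area (Los Angeles vs San Francisco Bay) in the social isolation, housing and race-interaction models. Keep a random intercept only if city is defined as many municipalities. The cost is one line in the model statement and one degree of freedom, with no new data beyond the area that the planned city term already requires.
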